### Statistical Methods

#### Randomization and Blinding

UPMC primary care practices serve as the unit of randomization, and all clinicians within a randomized practice receive the intervention assigned to that practice. We will stratify practice randomization by quartiles (25th, 50th, and 75th) of practice size based on preliminary practice data to balance the distribution of practice sizes across study arms. An additional covariate constraint on practice size will apply to further secure a balance across 3 arms in a 1:1:1 ratio due to the presence of large sites within the stratum [30,31]. The study statistician will generate randomization lists for each stratum using an SAS macro (SAS Institute) with varying block sizes. Once the randomized sequence is generated, only 1 designated member of the study team will receive the allocation list and embed it into the EHR system. Due to the nature of the intervention, treating clinicians are not blinded as they are exposed to EHR-based flags + nudges. Investigators and analysts will remain blinded to study arm assignment during outcome derivation and initial analyses using a prespecified analytic code that does not reference study arm labels. Study arm allocation will be revealed only after primary models are finalized for interpretation.

#### Sample Size and Power

We performed a priori power calculations using a simulation study designed to mirror the trial structure. The simulation incorporated 99 practices (created by regrouping the original 181 practices by size) and accounted for an unforeseen Epic system change that limited the intervention period to 4 months rather than the initially planned 6-month intervention period. The simulation used a multivariable proportional-odds linear mixed model and assumed an average of 8 eligible high-risk patients per clinical practice (range 2-16 across 1000 simulations), an intraclass correlation coefficient of 0.01, an estimated rate of the outcome from pilot analyses, and an anticipated 1– to 8–percentage point improvement in the primary composite outcome distribution from the usual care to the elevated risk flag plus nudge intervention arms, which is the a priori primary comparison for the study (Table 1). With 181 practices and a total sample size of 800 patients, the trial is estimated to have 81.3% power (α=.05) to detect the anticipated effect size between the elevated risk flag + nudges and usual care arms adjusting for a 1% attrition rate due to the development of malignant cancer or transition to hospice care after enrollment.

**Table 1 table1:** Outcome distributions assumed for power simulations for outcomes at 4 months (n=800).

Outcome			Usual care (%)		Elevated risk flag (%)		Elevated risk flag + nudges (%)
Naloxone			12		17.3		20.7
No high dose			90		91.3		92.7
No benzodiazepine overlap			94		94.7		95.3
**Overall distribution of ordinal composite outcome**							
	Score 3	10.1		14.7		18.1	
	Score 2	76.2		74.1		72.7	
	Score 1	13.2		10.8		8.9	
	Score 0	0.7		0.6		0.5	

#### Statistical Analysis

We hypothesize that primary care providers in clinics assigned to the elevated risk flag and behavioral nudges arm will demonstrate safer prescribing behaviors than those assigned to usual care (primary hypothesis) or elevated risk flag only (secondary hypothesis) arms.

The primary analysis will follow the intention‑to‑treat principle and CONSORT 2010 statement extension [32] using the target cohort of 800 patients. Any additional patients enrolled after the Epic system change will be included in secondary and sensitivity analyses. We will analyze the primary ordinal outcome at 4 months using a mixed‑effects ordinal logistic regression model with random intercepts for practice and fixed effects for study arm (elevated risk flag and elevated risk flag + nudges vs usual care). We will adjust for baseline outcome value (for evaluating changes in outcome scores in the analysis), practice size, and any additional baseline imbalanced covariates when appropriate. Secondary pairwise hypotheses will be evaluated only if the primary contrast (ie, elevated risk flag + nudges vs usual care) is statistically significant following a gatekeeping strategy to preserve an overall α at .05.

We will analyze secondary outcomes primarily using multivariable generalized linear mixed models with appropriate link functions, variable specifications, and distributional assumptions. We will also examine “off-target” effects among all patients seen in randomized primary care clinics, including low-risk patients not subject to the alerts but treated by clinicians who had seen alerts for other patients, as part of our secondary analyses.

Sensitivity analyses will assess robustness by varying outcome definitions (ie, using only prescription fill data vs only prescription order data), altering follow-up length (6 months rather than 4 months), conducting as-treated analysis for any arm crossover, and applying alternative eligibility criteria for prior OUD. We will introduce interaction terms for randomized groups by age, sex, race and ethnicity, baseline opioid MME, history of OUD, prior overdose, and psychiatric diagnoses and assess treatment heterogeneity effects.

Missing data are expected given the use of routinely collected EHR data and variability in clinical documentation and data completeness across practices. When applying the gradient boosting model to enrolled patients, missing predictor values are addressed using simple imputation procedures, with continuous variables imputed using median values and categorical variables imputed using mode values. The ordinal primary outcome will be computed from UPMC EHR data; however, some outcome components or covariates may have missing values. We will examine missing data patterns and compare baseline characteristics between participants with and without missing outcome data. When appropriate, we will implement multiple imputation with the fully conditional specification approach [33] or use joint modeling or shared parameter model approaches that simultaneously model the outcome and dropout or death as sensitivity analyses when appropriate.

Descriptive statistics will summarize practice-, clinician-, and patient-level characteristics by group. Statistical assumptions will be evaluated for each model, with corrective procedures applied when needed. Statistical significance will be determined using a 2-sided *P* value threshold of .05. Analyses will be conducted using SAS (version 9.4) and R (version 4.0.2; R Foundation for Statistical Computing).

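### The primary model would choose its extra covariates by observed baseline imbalance, under an undefined criterion, instead of from a named prognostic list

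*Protocol article*

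**What the plan says.** All of this is in the protocol article.

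- **Statistical Analysis, primary model.** The 4-month ordinal score is analysed by mixed-effects ordinal logistic regression with "random intercepts for practice and fixed effects for study arm".
- **Statistical Analysis, covariates.** Two are fixed. The first is the baseline score: "We will adjust for baseline outcome value (for evaluating changes in outcome scores in the analysis". The second opens the phrase at issue: "practice size, and any additional baseline imbalanced covariates when appropriate". No candidate variables, imbalance measure or threshold are given, and nothing says when adjustment counts as appropriate.
- **Statistical Analysis, testing order.** "Secondary pairwise hypotheses will be evaluated only if the primary contrast" (flag plus nudges against usual care) is significant. The level is two-sided .05.
- **Statistical Analysis, heterogeneity.** Seven baseline variables are named, for interaction terms only: "age, sex, race and ethnicity, baseline opioid MME, history of OUD, prior overdose, and psychiatric diagnoses".
- **Randomization and Blinding.** "Investigators and analysts will remain blinded to study arm assignment during outcome derivation and initial analyses using a prespecified analytic code", and "Study arm allocation will be revealed only after primary models are finalized for interpretation".

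**The concern.** Observed imbalance does not show which variables predict the outcome. A strong predictor that happens to be balanced stays out of the model and its precision gain is lost. A weak one that happens to differ goes in.

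The wording also leaves the primary model open until the baseline data have been compared by arm. Two careful analysts could finalise different models from the same data. In a logistic model the conditional odds ratio itself changes with the covariates included, so the quantity estimated would vary too. The primary test is also the gate for the secondary pairwise comparisons, so the choice carries through the testing sequence.

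**Working it through.** **1. Reproduce the plan's power figure.** Inputs from Sample Size and Power and Table 1: 800 patients in three arms, ICC 0.01, 1% attrition, and score distributions (3/2/1/0) of 10.1/76.2/13.2/0.7% for usual care and 18.1/72.7/8.9/0.5% for flag plus nudges. Each column sums to 100.2% and was rescaled. The common odds ratio fitted by maximum likelihood is 1.77 (log 0.569).

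Whitehead's formula: V = (N/12) × (1 − Σp̄³) / [1 + (m − 1) × ICC], and power = Φ(log OR × √V − 1.96). Here Σp̄³ ≈ 0.414.

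- N = 800 × 2/3 = 533, m = 800/181 = 4.42: power 81.4%.
- N = 533 × 0.99 = 528, m = 4.42: 81.1%.
- N = 528, m = 8: V = 44 × 0.586/1.07 ≈ 24.1, power 79.7%.

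The stated 81.3% is reproduced within 2 points without any extra covariates.

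**2. What adjustment could add, by formula.** Divide the residual variance by 1/(1 − R²), where R² is the variance explained beyond the two fixed covariates. The documents do not give it, so 0.05 to 0.20 is assumed. From 79.7%, power rises to 81.7%, 83.7% and 87.7% at R² of 0.05, 0.10 and 0.20.

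**3. Simulate the rules.** Two arms, 66 practices (two thirds of the 99 in the plan's simulation) of 8 patients, ICC 0.01, a linear score in place of the ordinal model, and a cluster-robust t test. There are seven independent, equally predictive candidates, matching the number in the interaction list. The outcome is read as what remains after the two fixed covariates. There were 4000 null runs, and 2000 with an assumed arm difference of 0.245 SD. Monte Carlo error is about 0.3 to 0.4 points for type I error and 1 point for power.

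Type I error (%):

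| Extra R² | None | All seven | Imbalance p<0.05 | p<0.10 | Std. diff. >0.1 | Most favourable of the five |
|---|---|---|---|---|---|---|
| 0.05 | 5.00 | 5.15 | 4.90 | 4.92 | 4.72 | 6.85 |
| 0.10 | 5.52 | 5.15 | 4.65 | 4.45 | 4.40 | 7.50 |
| 0.20 | 4.38 | 4.80 | 3.82 | 3.38 | 3.32 | 7.28 |

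Power (%):

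| Extra R² | None | All seven | p<0.05 | p<0.10 | Std. diff. >0.1 |
|---|---|---|---|---|---|
| 0.05 | 75.60 | 77.45 | 75.80 | 75.85 | 75.95 |
| 0.10 | 74.75 | 79.70 | 75.25 | 75.45 | 76.65 |
| 0.20 | 75.90 | 85.30 | 76.40 | 77.95 | 79.30 |

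The power levels depend on the assumed 0.245 SD; the differences between columns are what count. With the standardised-difference rule the loss against all seven is 77.45 − 75.95 = 1.5, 79.70 − 76.65 = 3.05 and 85.30 − 79.30 = 6.0 points. This is the mildest of the three cut-offs; at R² 0.20 the p<0.05 rule loses 85.30 − 76.40 = 8.9.

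Mean standard errors agree. At R² 0.10 the rule recovers (0.0909 − 0.0896)/(0.0909 − 0.0856) ≈ 25% of the available reduction, and at 0.20 (0.0921 − 0.0889)/(0.0921 − 0.0808) ≈ 28%.

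**4. Cross-check.** A simpler null simulation had 264 per arm, no clustering, and six covariates each correlated 0.15 or 0.25 with the outcome (6 × 0.15² = 13.5% or 6 × 0.25² = 37.5% of variance). Type I error was 5.0% and 3.7% for selection at p<0.05, 5.5% and 5.2% for the fixed set, and 7.6% and 8.5% for the most favourable model. The pattern is the same; the upper end rests on a large assumed R². A third version, with three arms and R² 0.05, gave 6.4% for the most favourable model.

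**The case against.** **The rule as written does not inflate type I error.** This stands. A reader might infer from the open wording that the 5% level is already lost. The simulations do not support that: any one imbalance rule applied mechanically gave 3.3% to 5.0%. The 7% to 8% figures describe fitting several models and reporting the most favourable, which the plan does not propose.

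**The blinding section is a safeguard.** This stands in part. A reader might see a contradiction with the promise of prespecified code. There is none: imbalance can be checked by coded arm, and the model finalised before allocation is revealed. That makes directional choice harder. But the same coded data also yield the primary p-value, so masking does not fix the model in advance.

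**A cut-off and candidate list may be in the analysis plan, which is not shown.** Also fair, and their absence from an article is not in itself a fault. What the article does state is the principle of selection by imbalance, and a cut-off supplied elsewhere would not change that.

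**The main predictors are already in.** Largely right. Baseline score is plausibly the strongest, and practice size is fixed too. Baseline MME overlaps with the dose component of the baseline score. The loss therefore concerns further covariates only and may lie at the low end.

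**Imbalance need not be chance here.** Practices are randomised, and patients enter later at a qualifying visit (Trial Design). The same trigger applies in usual care, which limits differences in patient mix but does not exclude them. Looking at imbalance is therefore reasonable; a sensitivity analysis is the place for it.

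**Conclusion.** The point holds as a matter of analysis choice. Selecting primary-model covariates by observed imbalance is an inferior rule to naming prognostic ones. It costs roughly 1.5 to 6 points of power at an assumed extra R² of 0.05 to 0.20 with a standardised-difference cut-off of 0.1, and more with stricter cut-offs. With planned power of 81.3%, the upper part of that range matters; at R² 0.05 the loss is small and close to Monte Carlo error.

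The undefined criterion is a separate and conditional risk: about 7% to 8% type I error in the worst case of favourable model choice, and none if a single rule is fixed and followed. The figures rest on assumed R² values, equally predictive independent covariates and a linear score standing in for the ordinal model. A reader might also infer that the power calculation is wrong. It is not: it is reproduced and does not depend on these covariates.

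**What to change.** - Delete the imbalance clause from the primary model.
- Keep baseline composite score and practice size, the latter in the form used in randomisation.
- Add a short named list chosen on subject-matter grounds from the variables already planned for the interaction analyses, for example age, sex, baseline MME, history of OUD, prior overdose and psychiatric diagnoses, with a brief reason for any left out.
- Put imbalance-driven adjustment in a sensitivity analysis with a stated measure and cut-off. This also covers differences in patient mix arising after practices were randomised.
- Primary-cohort analysis began in January 2026 (Results), so a list written now also follows data accrual. Date it before allocation is revealed and state what data, by coded arm or pooled, had been seen by then.

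The cost is about one sentence of text and a few more model parameters. No new data are needed beyond variables already planned for use.

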### Ethical Considerations

The clinical trial was approved by the University of Pittsburgh Institutional Review Board (IRB; STUDY22040068) on February 24, 2024, before trial initiation and is overseen by an independent data and safety monitoring board (DSMB). The study involves secondary analysis of limited EHR data from UPMC. In accordance with federal regulations and institutional policies, the IRB granted a waiver of patient informed consent and HIPAA (Health Insurance Portability and Accountability Act) authorization as the intervention poses minimal risk to participants and aligns with routine EHR-based clinical workflows. All analyses are conducted within the secure University of Pittsburgh Health Services Research Data Center server environment. This study complies with institutional data use agreements and all relevant guidelines and regulations for human subject research and data privacy. As this study involves secondary analysis of existing EHR data with no direct participant interaction no participant compensation was provided.

An independent institutional DSMB supported by the University of Pittsburgh Clinical and Translational Science Institute provides ongoing oversight. The DSMB held its initial meeting on December 6, 2024; reviewed the study design and charter; elected a chair; and approved the trial to begin. The DSMB is independent of the study investigators and funder and operates under a formal charter. The DSMB meets quarterly (or as needed) following trial initiation to review safety, protocol adherence, and study progress. Serious adverse events and unanticipated problems are to be reported to the DSMB chair and coordinators within 24 to 48 hours of investigator awareness and to the IRB per institutional policy. The DSMB may recommend continuation, modification, temporary suspension, or early termination of the trial.

## Results

This study was funded by the US National Institutes of Health in June 2022. Clinical trial enrollment began on March 10, 2025. Enrollment for the primary analysis cohort was completed (n=798) on May 26, 2025. Additional participants continued to be enrolled for secondary analyses (n=1662 as of December 12, 2025). Data analysis for the primary cohort began in January 2026, and results are expected by the middle of 2027.

## Discussion

We describe the protocol for a cluster randomized trial evaluating an ML-guided set of behavioral nudges embedded within the EHR to reduce overdose-related risk in primary care. We anticipate that this intervention will improve evidence-based prescribing behaviors associated with reduced overdose risks among elevated-risk patients and, in turn, reduce overdose risk. By integrating accurate risk prediction with actionable behavioral nudges, this study is expected to provide evidence on a scalable strategy to influence clinicians’ decision-making and improve opioid safety in real-world primary care settings.

Although prior studies have tested various prediction models for overdose [4,34-42] and others have examined behavioral nudging strategies to influence prescriber behavior [15,43-46], we are not aware of any prior randomized trials that test the combined impact of overdose risk prediction and behavioral nudges. Importantly, several overdose risk prediction tools have already entered clinical practice with limited validation and evaluation, underscoring the necessity of rigorous clinical trials to assess their real-world effectiveness and inform policy decisions. By testing these tools in practice in a large RCT, we will provide high-quality evidence on the effectiveness of these interventions, providing clinicians, health system leaders, and policymakers with critical data to guide adoption and implementation.

In designing the trial, we chose practice-level randomization rather than patient- or clinician-level randomization to minimize the risk of contamination across arms and ensure that all clinicians within practices received a consistent intervention. UPMC’s robust clinical informatics team and the presence of a large number of primary care practices operating on a unified EHR platform enabled this practice-level approach, allowing us to isolate the effect of the intervention alone on prescribing practices. Our months-long silent and live testing phases are a strength of the study, enabling calibration and refinement of the alerts to maximize predictive performance while minimizing excessive firing, workflow disruption, and alert fatigue. Although we anticipate that larger practices may generate a higher volume of alerts than smaller practices due to greater patient volume, our stratified randomization by practice size is designed to balance this difference across study arms. Our 3-arm design structure enables assessment of the added benefit of nudges over the risk flag alone.

There are some important potential limitations in this study. First, a challenge in designing trials addressing opioid overdose in primary care is the dynamic nature of how practices respond to the opioid epidemic and how the epidemic itself changes. For example, practices in our usual care arm could begin to adopt safer prescribing behaviors similar to those encouraged by our intervention if UPMC were to introduce parallel system-wide initiatives during the study period; however, we do not anticipate any major changes during our trial period. Other potential challenges include alert fatigue, variable clinician engagement, potential EHR system changes or updates, and model drift over time. We have mitigated these limitations through our iterative nudge design, model fairness and calibration assessments, continuous monitoring through silent and live phases, and proactive adaptation to systematic changes. Second, because overdose events are relatively rare, the trial is not powered to detect differences in overdose outcomes as a primary end point. Instead, we use a composite of prescribing behaviors with strong evidence linking them to reduced overdose risk as a pragmatic and actionable proxy [47]. Third, while we assigned study arm by practice to minimize the risk of contamination, some physicians and other clinicians may work out of multiple departments during the course of the study. Fourth, while our initial plan was for a 6-month intervention period, unexpected changes occurred in Epic within UPMC that required shortening the intervention period for the primary analysis to 4 months. However, we anticipate that most intervention effects will occur within the first four months of the trial, when clinicians receive the initial set of justification alerts. These alerts are programmed to reappear based on predefined criteria. Specifically, certain alerts will reappear 3 months after the index encounter if the underlying risk condition persists (eg, continued high opioid dosage or opioid/benzodiazepine overlap after a prior justification), whereas others reappear sooner if the triggering condition recurs (eg, a new opioid prescription). Regardless, we have preplanned a 6-month secondary outcome to compare any difference in intervention efficacy. Finally, we acknowledge that our intervention will focus on the primary care setting, and while it may generalize to other parts of the health care system that use an EHR, it will not help the many people at risk of overdose who do not engage with the health care system.

Our planned dissemination of study results includes the usual academic channels, including journal publication and presentation at scientific meetings in late 2026 and early 2027. We are also in regular communication with the clinical leadership of primary care in the health system, as well as the major informatics groups, enabling real-time dissemination of findings to interested parties who can implement changes after the clinical trial is completed. Our research team also received supplemental funding from the National Institutes of Health to compile “lessons learned” from our implementation and create a playbook that will guide others in implementing similar overdose prediction tools in the EHR in an ethical and successful manner.

In summary, the mPROVEN study is among the first pragmatic RCTs to integrate ML‑based opioid overdose risk prediction with behavioral nudges directly within a large health system EHR. By combining advances in data science, behavioral economics, and implementation science, the study aims to reduce opioid overdose risk in primary care using a scalable and low-touch intervention to address a high-priority public health issue.

